### 2.3. Project Design and Implementation

Institutions interested in participating in the project’s activities will be involved. The E-Walk project will be carried out in several sequential phases, aimed at identifying the key features/factors/characteristics influencing children’s engagement in physical activity through the use of a mobile application. Data collection will occur in two main phases. In Phase 1 (Section 2.4), group concept mapping will be used to identify key features and inform the design of the app and its in-app challenges. Phase 2 (Section 2.5) will assess the impact of the deployed app and challenges, with data collected at baseline and follow-up. Baseline measures will include questionnaires and anthropometric data, process measures will track app usage and challenge completion, and outcome measures will assess changes in physical activity, sedentary behavior, and BMI.

### 2.4. Phase 1: Development (Concept Mapping and App Design)

Standardized operating protocols will be implemented by the E-Walk team to ensure consistency in data collection. The concept mapping process will include four main phases to provide a wide range of perspectives and to strengthen the conceptual framework, as shown in Figure 1 [24]:Initial preparation: definition of the focus prompt.Generation, review, and validation of an exclusive feature/factor/characteristic list (minimum 45, maximum 130 exclusive features/factors/characteristics).Structural organization (sorting and rating): Stakeholders sort and rate features/factors/characteristics.Data analysis and interpretation: The final phase will involve both a quantitative and qualitative analysis of the generated sorting and rating data. Specifically, the analysis will synthesize the viewpoints of children and teachers into a conceptual framework reflecting the influence of different features/factors/characteristics that may positively or negatively affect engagement with and usability of a mobile application designed to support physical activity participation in primary school students.

#### 2.4.1. Initial Preparation

In this phase, the focus prompt will be finalized to facilitate participant recruitment and stimulate idea generation during brainstorming activities. The proposed prompt will be

“What do you think could be the features, factors or characteristics that may influence, in a positive or negative way, the engagement and usability of a specific mobile app to participate in physical activities by primary school students?”

#### 2.4.2. Generation, Review, and Validation of an Exclusive Statement List

A comprehensive list of features/factors/characteristics will be gathered from brainstorming sessions involving children and teachers. These will be organized into a structured list of relevant features/factors/characteristics, representing potential influences on engagement with and usability of the mobile app. Online brainstorming sessions will be distributed across the eight European Union countries involved in the project, using networks of schools and professional associations.

To analyze the open-ended responses of the brainstorming phase, three researchers will create an initial codebook based on the focus prompt answers. Subsequently, two researchers will independently code each participant’s response, refining the codebook as necessary. This review will aim to ensure clarity, avoid repetitions, and decide whether any of the identified features/factors/characteristics need to be further broken down. Expert researchers with a deep knowledge of the subject area and a good command of English will be invited to evaluate and provide insights on the features/factors/characteristics. Each feature/factor/characteristic will be evaluated using a 5-point Likert scale, ranging from 1 (unclear) to 5 (clear), to assess its clarity. Researchers will have the opportunity to comment on the relevancy, representativeness, ratability, and saturation of each feature/factor/characteristic. This feedback will help to refine and enhance the quality of the list. In accordance with established guidelines, each feature/factor/characteristic that receives an evaluation score below 3 will be revised to improve clarity or entirely removed from the list [28]. Discrepancies will be discussed collaboratively until a consensus is achieved with the supervision of a third researcher. After completing the processes, a comprehensive and exhaustive list will be uploaded to Concept Systems software (Concept Systems, Incorporated, NY, USA, version: build 2022.273.21) for the subsequent structuring phase (sorting and ratings).

#### 2.4.3. Structural Organization (Sorting and Rating)

The structuring phase will comprise two distinct activities: sorting and rating. Upon providing participant information and consent, participants will be presented with the final list of features/factors/characteristics in a random sequence via the Concept Systems online platform.

Initially, the features/factors/characteristics will be presented in a random order, and the participants will use the Concept Systems software to categorize the features/factors/characteristics identified in the generation phase by sorting them based on perceived similarities. Each feature/factor/characteristic will be labeled with a unique code to indicate its origin, whether from the teachers, students, or other stakeholders. Participants will also be provided with an identification code to guarantee a consistent uniform interpretation. Each feature/factor/characteristic will be included in only one category/pile, and participants will be encouraged to sort the factors into a minimum of 6 to maximum of 14 categories/piles. Each category will be named to reflect its theme or content. Each feature/factor/characteristic will be assigned to only one category, ensuring that no feature/factor/characteristic will belong to multiple categories. If a feature/factor/characteristic appears distinct or unique, it could stand alone within its own category.

The rating phase will be conducted via an online survey in which participants will rate each feature/factor/characteristic on two six-point Likert scales: usability (1 = not usable, 6 = very usable) and level of engagement (1 = not engaging, 6 = very engaging).

#### 2.4.4. Data Analysis and Interpretation

Before starting the data analysis, one of the co-authors with certified expertise in the concept mapping procedure will review the participants’ sorting and rating responses to confirm their adherence to the provided guidelines. Descriptive statistics including mean, standard deviation, and frequency of occurrence will be calculated for both demographic data and feature/factor/characteristic rankings. Subsequently, the GroupWisdom™ online platform will be used for data analysis, employing a square symmetric similarity matrix generated from the sorted features/factors/characteristics. A two-dimensional non-metric multidimensional scaling technique will be applied, mapping each feature/factor/characteristic as a point on an x-y spatial “point map” for each cohort. Hierarchical cluster analysis will be utilized to cluster the points representing each feature/factor/characteristic on the point maps. For the children, teachers, and different stakeholders involved, the E-Walk project team will assess various cluster solutions following the recommended steps by Kane and Trochim [29] with the objective of collapsing clusters logically to emphasize distinct themes among the features/factors/characteristics. This process represents a mixed-method approach to the data analysis, blending the quantitative statistical outcomes with a qualitative interpretation by the project team. Then, clusters will be named based on category names provided by participants during the sorting phase and the consensus of the project team. Go-Zones will be established once the cluster maps are agreed upon and finalized, showcasing feature/factor/characteristic ratings on usability and level of engagement in relation to mean ratings. The top-right quadrant (green—IV) of the Go-Zone will comprise features/factors/characteristics considered both more important and more engaging than the average. Features/factors/characteristics and clusters identified in the concept map will be considered as candidate items (and groups) for inclusion in future reporting guidelines for concept mapping research [30].

### 2.5. Phase 2: Evaluation (Deployment and Impact Assessment)

The concept mapping procedure will be used to identify features/factors/characteristics that make a mobile app easy, enjoyable, and useful for encouraging physical activity among children based on the perspectives of primary school students, schoolteachers, physical activity stakeholders, and relatives and guardians [17]. In addition to informing the app’s design and usability features, the concept mapping approach will also guide the development of educational content as well as content related to physical activity and sport, ensuring that it will be aligned with the needs, preferences, and motivational drivers of these target groups. Once the mobile app and the sport activities (i.e., routes, tasks, challenges) are developed, students and other stakeholders will walk, run, hike, or roll along selected routes while engaging with educational and sport content derived from the concept mapping results. Feedback and user characteristics will be assessed as detailed in Section 2.5.1 and Section 2.5.2.

In line with the study’s objectives, specific success indicators will be used to evaluate the impact of the intervention. Primary indicators will include changes in physical activity metrics such as daily step count, minutes of moderate-to-vigorous activity, and reductions in sedentary time, as recorded through app-based measures and validated questionnaires. Physical activity levels will be assessed using the Physical Activity Questionnaire for Older Children (PAQ-C) [31] for children (students aged 9–15 years) and the short version of the International Physical Activity Questionnaire (IPAQ) [32] for teachers (adults aged ≥ 18 years old). The PAQ-C is a self-administered tool for children, providing a score from 1 (low activity) to 5 (high activity) based on nine items. The tenth item, related to illness, is not included in the final score. The PAQ-C has been validated in different countries and cultural contexts, demonstrating good reliability for assessing self-reported physical activity among school-aged children [31]. It has been translated into multiple languages and adapted to local habits (e.g., types of common sports or leisure-time activities), which makes it suitable for use in our multinational study context. The IPAQ includes 7 items assessing frequency, intensity, and duration of physical activity, along with sitting time. It includes both categorical (inactive, minimally active, HEPA active) and continuous scores (MET-minutes/week) [33,34]. The IPAQ has been validated for adults in more than 20 countries, with standardized translations and cultural adaptations [32]. In addition, anthropometric parameters will be collected as complementary success indicators to monitor changes in body composition and overall health status during the project. Weight and height will be determined using a precision instrument that combines a scale and stadiometer accurate to 0.1 kg and 0.1 cm (Seca, model 709, Vogel & Halke, Hamburg, Germany). Additionally, the BMI will be calculated. Both physical activity levels and anthropometric data will be evaluated for the entire three-year duration of the project.

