Group concept mapping is a structured participatory methodology that systematically collects, integrates, and visually represents stakeholders’ perspectives [17]. By combing qualitative and quantitative methods [18,19,20,21,22,23], it enables the identification and prioritization of features that influence the usability of and engagement with health interventions [24]. Previous research supports that applying concept mapping in youth contexts [25] can reveal children’s genuine motivators (e.g., playful route expansions, scoreboard rivalry, cross-curricular quizzes) while also clarifying teacher concerns (e.g., limited time, alignment with academic schedules).

Given the increasing integration of smartphones and tablets into children’s daily routines, and the growing use of mobile applications for health promotion, it is essential to identify the features that make these tools engaging, accessible, and useful. Group concept mapping provides a structured way to achieve this by systematically incorporating the perspectives of primary school students, teachers, physical activity stakeholders, and families.

Within the Walk around the Earth (E-Walk) project [26,27], this participatory approach will first aim to identify the most influential factors affecting engagement with and usability of a mobile application designed to support physical activity in primary school students. Based on these insights, the project will then develop and refine a step-based app integrating educational and physical activity content, and subsequently evaluate its impact on (i) physical activity metrics (e.g., daily steps, minutes of activity), (ii) anthropometric parameters such as Body Mass Index (BMI), and (iii) changes in physical activity classification. Overall, the project seeks to address one of today’s most pressing health challenges by developing an intervention that combines physical activity, digital technologies, and learning opportunities, thus making physical activity more engaging and enjoyable.

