### 2.2. Participants and Inclusion/Exclusion Criteria

Participants will include primary school students aged 9 to 15, schoolteachers, physical activity stakeholders, and relatives or guardians. Students will be subsequently divided into two age groups (9 to 12 and 13 to 15). Inclusion will be restricted to those regularly enrolled in primary schools and able to read and understand the language of the validated questionnaires used in each country. Only children with access to a compatible mobile device, either personal or shared, will be admitted. Those with medical conditions or physical disabilities that contraindicate moderate-to-vigorous physical activity, or with cognitive or developmental impairments that prevent them from comprehending the app content or questionnaire items, will not be eligible.

Teachers will be eligible if employed at one of the participating schools or directly involved in school activities. They must be able to complete the questionnaires and engage with app-related tasks, possessing sufficient digital literacy to use a smartphone or tablet. Adults with severe health conditions preventing participation in physical activity or those unable to engage with digital tools will be excluded.

Parents, guardians, and other stakeholders will be included if directly involved in supporting children’s education or physical activity and available to participate in focus groups, surveys, or feedback activities related to the intervention. Those lacking sufficient access to digital devices and literacy to engage with the app-based activities will be excluded.

Recruitment will take place through workshops organized in one or more local schools, ensuring a diverse range of ages and socio-cultural backgrounds. Participation will be voluntary, and all participants will be fully informed about the project and its aims. They will be allowed to withdraw from the study at any time without consequences. Written informed consent will be obtained from the participants. For children, written parental consent will also be required. In accordance with Regulation (EU) 2016/679 of the European Parliament and Council on the protection of personal data (General Data Protection Regulation), each participant will be assigned an anonymous identification code. All collected data will be used exclusively for statistical and research purposes.

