### 2.6. Statistical Analysis

The evaluation phase of the project will adopt a quasi-experimental pre-post design without randomization. Children and schools will first participate in the baseline assessment (anthropometric data, PAQ-C/IPAQ, app usage, and engagement metrics), followed by the implementation of the mobile app and sport activities. Post-intervention assessments will be conducted at multiple time points (e.g., 6 months and 12 months after implementation) to examine changes in physical activity levels, sedentary behaviors, and anthropometric outcomes relative to baseline. The statistical methods and analyses that will be applied to investigate the effect of the mobile app, specifically designed based on a concept mapping approach, on physical activity engagement and educational interaction in primary school students are specifically detailed in Supplementary File S1 [35,36].

All analyses will be performed using STATA 18 (StataCorp LP, College Station, TX, USA).

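### Change in children's BMI is an outcome with no age and sex standardisation, so expected growth is mixed with any app effect

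*Protocol article*

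**What the plan says.** BMI enters the protocol article as an outcome in several places. The Introduction lists, among the effects to be evaluated, "anthropometric parameters such as Body Mass Index (BMI"). Section 2.3 states that "outcome measures will assess changes in physical activity, sedentary behavior, and BMI". Section 2.5 gives the rank and purpose: "anthropometric parameters will be collected as complementary success indicators to monitor changes in body composition and overall health status during the project". It then describes how weight and height are measured and adds "Additionally, the BMI will be calculated".

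The population is set in section 2.2: "Participants will include primary school students aged 9 to 15, schoolteachers, physical activity stakeholders, and relatives or guardians". The contrast is set in section 2.6: "The evaluation phase of the project will adopt a quasi-experimental pre-post design without randomization". The timing is "Post-intervention assessments will be conducted at multiple time points (e.g., 6 months and 12 months after implementation"), and the comparison covers "sedentary behaviors, and anthropometric outcomes relative to baseline". No control group is described.

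Section 2.1 allows age to enter the analyses as a covariate or through age strata, because motivation, development and activity differ across the age range. The Discussion adds that gender should be considered in design and analysis. Neither provision is tied to BMI. Section 2.6 refers the statistical methods to Supplementary File S1, which was not available for this review.

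**The concern.** Between 9 and 15 years BMI normally rises, at a rate that depends on age and sex. With each child as their own comparator and no concurrent group, the change in kg/m² has two parts: the growth that would have occurred anyway, and whatever the app adds or removes. The design as described cannot separate them.

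If the app does nothing, the expected result is a rise in BMI. If it has a modest benefit, the expected result is still a rise, only smaller. The Conclusions section expects the evaluation to show whether growth becomes healthier, and an unstandardised pre-post change in BMI cannot show that.

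A smaller point concerns wording. Section 2.5 presents these measurements as tracking body composition. Weight and height give weight status; they do not distinguish fat from lean mass.

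**Working it through.** The article states no sample size, SD, growth rate, effect size or test for BMI, so there is no figure of its own to reproduce. What follows is an illustration.

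**Inputs from the article:** ages 9 to 15 (section 2.2); pre-post comparison with own baseline, with 12 months as one of the example visits (section 2.6).

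**Assumed inputs, none from the article:** natural BMI growth g = 0.3, 0.5 or 0.8 kg/m² per year; SD of 12-month change s = 1.0 or 1.5 kg/m²; n = 100 or 200 children; paired t-test, two-sided 5%.

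**Step 1. Expected change.** Mean change = g × t − b, where t is years since baseline and b is the true benefit. At t = 1 and b = 0 this is +0.3 to +0.8 kg/m².

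**Step 2. Chance of a significant rise when the app has no effect.** The noncentrality is (g × t) / (s/√n). For n = 100, s = 1.5, g = 0.3: SE = 1.5/10 = 0.15, and 0.3/0.15 = 2.0, against a critical value of about 1.98. The chance is therefore close to one half.

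| n | SD | g = 0.3 | g = 0.5 | g = 0.8 |
|---|---|---|---|---|
| 100 | 1.5 | 0.508 | 0.910 | >0.999 |
| 100 | 1.0 | 0.844 | 0.999 | 1.000 |
| 200 | 1.5 | 0.804 | 0.997 | 1.000 |
| 200 | 1.0 | 0.988 | 1.000 | 1.000 |

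The range is about 50% to 100%. With no drift, a significant rise would occur in 2.5% of studies. Fewer children lower the figure: n = 50, SD 1.3 and g = 0.3 gives about 37% by normal approximation.

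**Step 3. A true benefit of b = 0.2 kg/m² at 12 months.** Mean change is 0.3 − 0.2 = +0.1, 0.5 − 0.2 = +0.3, or 0.8 − 0.2 = +0.6. For n = 100 and SD 1.0, a significant rise has probability 17%, 84% and about 100% respectively, and a significant fall has probability 0.2% or less. The mean change is negative only if b exceeds g × t.

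**Step 4. Does the age provision in section 2.1 remove this?** Baseline age as a covariate, or the strata 9 to 12 and 13 to 15, adjusts for differences between children. The problem is each child's own growth between visits, which is present in every stratum and coincides with time since baseline. Age at each visit in a longitudinal model is different, because age differences between children then inform the growth slope. A simulation with no app effect, linear growth of 0.5 kg/m² per year, n = 200 and SD of change 1.2 (all assumed) bears this out. The paired test rejected in 100% of 200 runs. A mixed model with age at visit rejected in 7%, with a mean post-app estimate of −0.02. This relies on growth being correctly modelled and on older and younger children differing only by age.

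**Step 5. After standardisation.** With BMI-for-age-and-sex z-scores, the expected change under no app effect is about 0 at every visit, provided the reference fits the population. The term g × t drops out of the contrast.

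**The case against.** The strongest reply is that the article never says raw or kg/m². BMI has to be calculated before any z-score can be, the same paragraph covers adults, and the analysis methods are deferred to Supplementary File S1, which may standardise BMI for children. This stands as a limit on confidence: a reader might infer that the full plan certainly analyses raw BMI, and the article alone does not show that. It does not remove the point. The article itself names the outcome as BMI in several places and sets the contrast as change from baseline, without qualification for children.

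A reader might also infer that adjusting for age can never help. That is too strong, as step 4 of the working shows. But section 2.1 does not say age at visit, does not link the adjustment to BMI, and offers stratification as an alternative.

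A third inference would be that growth hides any benefit at all. It hides only benefits smaller than the growth over the interval; a larger one would still appear as a fall.

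It is also fair to say that section 2.5.1 relates the anthropometric data to children's growth, so growth is recognised, and that the Discussion asks for gender to be considered. Neither statement separates growth from an app effect. Finally, the three-year observation is the duration of the whole project, which includes app development. Three years of growth after the app starts is therefore not established, and the calculation stops at 12 months.

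**Conclusion.** The point holds for a complementary outcome. As the article words it, change in students' BMI from baseline combines expected growth with any app effect, and nothing in the described design separates the two. The direction of the bias requires only that BMI normally rises at these ages. Its size, a significant 12-month rise in about 50% to 100% of studies with an ineffective app, depends on the assumed growth, SD, sample size and simple paired test. A reader might prefer the narrower range of 80% to 100%, but that applies only at 200 children, and the article fixes no sample size.

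The primary indicators (steps, activity minutes, sedentary time) are not affected. Confidence is moderated by File S1, which could already define a standardised measure; in that case the article's wording needs to be brought into line with it.

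**What to change.** In sections 2.3 and 2.5, state that for students the anthropometric outcome is change in BMI-for-age-and-sex z-score, computed from exact age at each measurement against one named growth reference. Check that Supplementary File S1 says the same. Report unstandardised BMI descriptively for students and keep it for adults. In section 2.5, replace the reference to body composition with weight status.

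The cost is a few sentences and a standard conversion. Weight and height are already measured, and exact age and sex are simple demographic fields. The change should be made before the data are analysed. It does not supply a comparison group: secular trend and regression to the mean remain, and the BMI result should be reported with that caveat.
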